### Inclusion criteria

We will include all RNs on the control ward and intervention ward in accordance with what is stated above. We will include patients with a cancer diagnosis who are aged 18 years and older and who are cognitively intact and able to communicate verbally. We will establish the presence of cancer-related pain for the last 24 hours using the VAS [26] at time of admission or no later than within the first 24 hours following admission. Patients with a score of > 1 on the VAS will be invited to participate.

### Exclusion criteria

RNs coming to work on the intervention ward or control ward as temporary staff will be excluded from participating in the study. We will exclude patients admitted onto the ward because of trauma or planned and/or acute surgery.

#### Intervention programme

Our intervention will focus two key components: (1) a theory-based education for ward RNs caring for patients with a cancer diagnosis and (2) the introduction and implementation of guidelines for daily, systematic pain assessments for those patients on the wards suffering from cancer-related pain.

##### (1) Education - workshops

The educational intervention for nurses will be arranged in the form of workshops. In this study we have defined the concept of workshop as an interactive activity aimed at promoting learning about a pre-set subject or topic. Workshops are said to support the participants in the process of jointly creating insight, knowledge and understanding. It is a democratic and social process [19] created by the interactions that occur between the facilitator and those participating. This results in all competencies present acting as resources in the creation of learning.

The content of the workshops will be based on the Scottish Intercollegiate Guidelines Network for the treatment of cancer pain in adults [27], and on the literature search performed for this study. As we are aiming for sustained behavioural change among the RNs the curriculum for the workshops will be developed from the Theory of Planned Behaviour [19]. Consequently, the curriculum will include the three distinct elements - beliefs about the likely impact of the behaviour, beliefs about the normative expectations and beliefs about the factors that help or hinder behaviour - which Ajzen [19] suggests controls human behaviour. Importantly, TPB describes intention as the combined result of the three elements i.e. the individual's attitudes, subjective norms, and perceived behavioural control. If these are generally positive, the individual will have the intention of performing the behaviour and if the behaviour is beyond the individual's control the behaviour does not occur. Perceived behavioural control thus has a direct impact on behaviour. As a result, the training in the workshops will focus on these components to achieve greater intention (Figure 2).

**Figure 2 F2:**
[figure not shown]
**Overview of theory based intervention - workshops**.

The educational intervention consists of a set of workshops (180 minutes each) and each workshop will include 15 RNs from the intervention ward. The first workshop will comprise sessions on pain anatomy, physiology and pain analysis through case study discussions. The second workshop will comprise subjects such as different treatments for cancer-related pain and case study discussions (Figure 2). The workshops will be conducted partly in working groups but also as free discussions in the group as a whole. According to Ajzen [28], persuasive communication theory can also be used to change a form of behaviour. To maintain possible positive behaviour following the intervention, reminder tags will be set up on a regular basis to inform nurses about the most recent guidelines for pain management.

##### (2) The implementation of guidelines concerning daily systematic pain assessments

Guidelines for pain management and systematic pain assessment will be implemented on the intervention ward immediately following the educational intervention. The daily pain assessment will be integrated as a required standard parameter together with the ordinary routine vital parameters such as temperature, pulse and blood pressure. Routine vital parameters on the wards are performed by RNs representing three different work shifts and pain will thus be assessed by the VAS at three points in time i.e. 4 am - 6 am, 1 pm - 3 pm and 7 pm - 9 pm. Pain intensity, nursing action and nursing follow up will be documented in the patient-specific study protocol at the bedside.

VAS is an instrument consisting of a 10 cm horizontal line, which measures pain intensity from "no pain to "worst pain imaginable". Patients participating in the study will be asked to assess current pain intensity by marking the line between the two extremes [26]. The average test-retest coefficient across four studies involving adults with cancer-related pain was r = 0.80 [29]. VAS can be used as a regular, short-term assessment instrument for pain intensity as well as an evaluation of ongoing pain treatment [30].

#### Control intervention - usual care

Patients with a cancer diagnosis admitted to the control ward will receive the usual care from their RNs, i.e. care for their patients according to normal practice.

#### Outcome parameters

##### Primary outcome measure

Our primary outcome will be RNs' attitude and knowledge as measured using a modified version of the KAS [31] at baseline, four weeks and twelve weeks after the intervention for the RNs on the intervention ward (Figure 1). As there is a risk that the RNs on the control ward may be inadvertently exposed to the interventions, i.e. assessing their patients' pain intensity and pain impact on daily life, the RNs on the control ward will also be assessed at baseline and at twelve weeks to check for exposure biases.

The original KAS consists of 40 items where items 1-22 are false-true statements, items 23-36 are multiple-choice questions and items 37-40 consist of two case studies [31]. KAS has shown test-retest reliability (r > 0.80) [31] and internal consistency [32] range between 0.70 - 0.73 [31,33]. KAS takes around 10-15 minutes to complete and the number of correct answers is divided by the number of items (38) to produce the percentage of the total score [31]. We have removed two items as they were considered to be context-specific for the instrument's country of origin. The instrument has not been used in Sweden previously, hence a back translation by an authorised translator from English to Swedish was made.

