**Methods/design:**

A quasi-experimental study design will be used to investigate whether the implementation of guidelines for systematic daily pain assessments following a theory-based educational intervention will result in an improvement in knowledge and attitude among nurses. A further aim is to investigate whether the intervention that targets nurses' behaviour will improve hospital patients' perception of pain. Data regarding nurses' knowledge and attitudes to pain (primary outcome), patient perception regarding pain (secondary outcome), together with socio-demographic variables, will be collected at baseline and at four weeks and 12 weeks following the intervention.

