### Setting, sample and sample size considerations

Participants (i.e. patients and RNs) will be recruited from two surgical wards specialising in patients with a cancer diagnosis at a hospital in South East Sweden. The hospital has 370 beds and provides services for approximately 150,000 people in the region. The intervention and control ward (26 beds on each ward) has 70 RNs and each year the wards admit around 820 patients who have been diagnosed with cancer.

Following negotiations on all organisational levels, both wards have agreed to participate in the study. The reason for this optimal numbers of participating RNs (n = 70) is that this study is seen within the organisation as providing support to the staff's annual education slots but also as part of supporting quality assurance of its care provision. Assignment to either the intervention ward or control ward is done by the research team.

Sample size calculations for the primary outcome measured by the Knowledge and Attitudes Survey Regarding Pain (KAS) are based on an expected 4.8 change in scores [24] among the RNs on the intervention ward and no changes among the RNs on the control ward. A significance level ᾳ of 0.05 (two-sided) and a power of 80% would require 33 RNs per group. Sample size calculations for the secondary outcome measure, the BPI-SF are based on the expectancy of a 1, 8 point decrease in total score regarding item current pain intensity among the patients on the intervention ward compared to the patients on the control ward [25]. Based on a significance level ᾳ of 0.05 (two sided) and a power of 95% this would require 30 patients per group.

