### Statistical analysis

Comparability between intervention and control groups will be assessed at baseline and at end of study to check for differences between participants, i.e. RNs and patients. Outcomes (KAS and BPI-SF) together with variables such as demographics, diagnosis, age, RN's length of experience and education, both at baseline and at end of study, will be compared between the intervention and control groups using both univariate and multivariate techniques [44]. Data will be analysed in accordance with the intention-to-treat principle. All participants with valid data regardless of whether they remained in the setting at baseline, drop-outs and losses to follow-up will be described.

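### The control ward sits no KAS at four weeks, so the four-week change in the primary outcome is uncontrolled and the intervention ward has one extra sitting of the test before week 12

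*Protocol article*

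**What the plan says.** Four places in the protocol article bear on this.

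- **Primary outcome measure.** The KAS is taken "at baseline, four weeks and twelve weeks after the intervention for the RNs on the intervention ward". For the other ward, "the RNs on the control ward will also be assessed at baseline and at twelve weeks to check for exposure biases". The stated worry is that control nurses might be exposed to the intervention by accident.
- **Abstract, Methods/design.** Data on nurses' knowledge and attitudes, on patients' pain and on socio-demographic variables "will be collected at baseline and at four weeks and 12 weeks following the intervention". No difference between wards is mentioned.
- **Statistical analysis.** KAS and BPI-SF, with background variables, "both at baseline and at end of study, will be compared between the intervention and control groups". No between-ward comparison at four weeks is described.
- **Setting, sample and sample size considerations.** The KAS calculation is "based on an expected 4.8 change in scores [24] among the RNs on the intervention ward and no changes among the RNs on the control", that is, on the comparison ward. With a two-sided 5% level and 80% power this gives 33 nurses per group. The two wards together have 70 nurses.

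**The concern.** Four weeks is one of only two post-intervention time points for the primary outcome, and only one ward is measured there. A rise at four weeks can be judged only against that ward's own baseline. It could reflect the workshops, familiarity with a questionnaire already seen once, or anything else that happened over the period. The section on study design justifies a control group as the means of separating the intervention from extraneous influences, and at four weeks that means is absent.

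The second consequence falls on week 12. By then the wards differ in the intervention and also in how often they have sat the test. If a further sitting improves the score, the gain falls on the trained ward alone. Adjustment for baseline cannot remove it, because the extra sitting coincides exactly with ward. The four-week test might also act as a refresher shortly before a measurement meant to show whether improvement lasts.

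The wards are not randomised, and the article accepts that they may differ systematically. That is a reason to avoid adding a further difference that is within the team's control.

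**Working it through.** **Step 1. Count the sittings** (from the primary outcome section).

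| KAS sitting | Intervention ward | Control ward |
|---|---|---|
| Baseline | yes | yes |
| Four weeks | yes | no |
| Twelve weeks | yes | yes |
| Sittings up to and including week 12 | 3 | 2 |

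Of the two post-intervention time points, only week 12 has a control value. The baseline sitting is common to both wards, so its retest effect should largely cancel at week 12. What remains is the marginal effect of a third sitting over a second.

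**Step 2. Recover the SD behind the sample size.** The article gives a difference of 4.8, two-sided alpha 0.05, 80% power and 33 per group, but no SD. The 33 can therefore only be back-solved, not independently reproduced.

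- Normal approximation: SD = 4.8 × √(33/2) / (1.960 + 0.842) = 6.96.
- Two-sample t-test (noncentral t, n = 33 per group): SD = 6.85, a standardised difference of 4.8/6.85 = 0.70.

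I use 6.85 below; 6.96 gives the same rates after rounding to a whole per cent.

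**Step 3. Effect of an assumed retest gain at week 12.** Suppose there is no true effect, and the extra sitting adds b points on the intervention ward only.

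- Standard error of the difference: SE = 6.85 × √(2/33) = 1.686.
- Probability of a two-sided 5% rejection: Φ(b/SE − 1.96) + Φ(−b/SE − 1.96).

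| Assumed b (points) | b as share of 4.8 | b/SE | False-positive rate |
|---|---|---|---|
| 0 | 0% | 0 | 5% |
| 0.5 | 10% | 0.30 | 6% |
| 1.0 | 21% | 0.59 | 9% |
| 1.5 | 31% | 0.89 | 14% |

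A different SD moves the upper end: for b = 1.5, an SD of 6 gives 17% and an SD of 8 gives 12%.

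**Step 4. Units.** The article scores the KAS as correct answers divided by 38 items, expressed as a percentage, so one item is 100/38 = 2.6 percentage points. It does not say whether the 4.8 is on that scale. If it is, 1.5 points is 1.5/2.6 = 0.6 of an item. If the 4.8 is a raw count, 1.5 points is one and a half items. The rates in step 3 hold either way, provided b and 4.8 share a unit, but the plausibility of a given b depends on which it is.

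**The case against.** The planned between-ward analysis uses baseline and end of study, and both wards have KAS data at each. Nothing in the article announces a between-ward test at four weeks. A reader might infer from the schedule that the primary comparison lacks a control, and the documents do not support that.

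A reader might also infer that the 12-week contrast is biased. That again goes too far. No passage reports a practice gain on the KAS or says that nurses are given the answers. Both wards will have seen the test once at baseline, and a third sitting may add less than a second. At the low end of the assumed range the error rate is about 6%, close to nominal.

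The inconsistencies in wording are mild. The abstract pools several kinds of data in one sentence and omits an exception; it does not say that both wards are tested at four weeks. Using the control ward's KAS both as a contamination check and as comparator is workable, since a rise on that ward would be informative for both purposes.

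Finally, another sitting on the control ward adds contact with pain content where the article wants to limit it. If one sitting matters on one ward, it may matter on the other.

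These points lower the severity and make the bias potential, not shown. They leave two facts in place: the four-week change has no control, and test exposure before week 12 is unequal by an explicit rule.

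**Conclusion.** The point holds in a limited form. The four-week KAS change is uncontrolled and can support only a within-ward description. The 12-week contrast is controlled but may lean towards the intervention. Under an assumed gain of 0.5 to 1.5 points from the extra sitting, its false-positive rate would be about 6% to 14% instead of 5%.

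That range rests on four assumptions: the size of the gain, which the documents do not give; an SD of about 6.85, back-solved from 33 per group; a gain in the same units as the 4.8; and wards that are otherwise comparable with independent nurses, which a non-randomised two-ward design does not guarantee. The sample size is not in dispute here, and equal testing would leave it at 33 per group.

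Severity: should be fixed, as a cheap improvement. It is not a fault that invalidates the study.

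**What to change.** Preferred: give the control ward the KAS at four weeks, at the same time as the intervention ward. With 70 nurses on two wards, an even split (an assumption) means about 35 extra questionnaires. At the article's 10 to 15 minutes each, that is 35 × 10/60 = 5.8 to 35 × 15/60 = 8.8 nurse-hours. The price in design terms is one more exposure to pain content on the control ward, which the article should accept openly. It has to be settled before the four-week visit, because the missing values cannot be collected afterwards.

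Alternative: drop the four-week KAS on the intervention ward. This also equalises exposure, at the cost of the early measurement.

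If neither is done:

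- name the between-ward difference in KAS at 12 weeks as the primary contrast;
- report the four-week data as uncontrolled and descriptive;
- acknowledge the unequal number of sittings as a limitation of the 12-week result, since labelling alone does not remove it;
- align the abstract with the primary outcome section.

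The text changes amount to a sentence or two in the abstract, the primary outcome section and the statistical analysis section.

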##### Secondary outcome measure

We will measure pain intensity and pain impact on daily life among the patients using the Brief Pain Inventory - Short Form [34]. The patient assessments by BPI-SF on admission (or no later than 24 hrs after admission) to the wards (intervention ward and control ward) and on discharge from the wards will follow directly after the educational intervention for the RNs on the intervention ward and control ward (Figure 1). The BPI-SF will be undertaken by the RNs admitting, discharging and/or responsible for the patient. Our rationale for including assessments of the patients on the control ward is our wish to rule out competing explanations for results obtained [23], i.e. a positive change in the patients' pain perception on the intervention ward. Hence, both groups will be compared in terms of secondary outcome, demography and diagnosis.

BPI-SF is a pain assessment instrument developed for cancer patients [34]. It is widely used and demonstrates sound psychometric properties [2,4,35-42]. The Swedish version has been linguistically validated but has not yet been psychometrically validated [43]. The instrument consists of nine items, as well as a figure depicting a human body where the patient marks the location and type of pain. BPI-SF includes items relating to the current degree of pain, pain during the last 24 hours and pain on average, as well as items related to the effect of pain treatment, walking ability, mood, work, relationships and whether sleep is affected by pain [34].

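### The abstract and the methods give incompatible schedules for the patient pain outcome, and under the methods schedule neither ward has a pre-education patient level

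*Protocol article*

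**What the plan says.** The protocol article describes the timing of the patient outcome in three places.

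- **Abstract, Methods/design.** One sentence covers the nurse outcome and "patient perception regarding pain (secondary outcome), together with socio-demographic variables", and says that these data "will be collected at baseline and at four weeks and 12 weeks following the intervention".
- **Secondary outcome measure.** BPI-SF is completed "on admission (or no later than 24 hrs after admission") and again at discharge, on both wards. The assessment at admission and that "on discharge from the wards will follow directly after the educational intervention for the RNs on the intervention ward and control ward". No patient assessment before the education is mentioned, and none at 4 or 12 weeks. The 4- and 12-week times recur only for the nurses' KAS, under Primary outcome measure.
- **Statistical analysis.** KAS and BPI-SF are compared between groups at baseline and at the end of the study. For patients, the section does not say whether baseline means before the education or at admission.

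Three other statements bear on this. The pain-assessment guidelines "will be implemented on the intervention ward immediately following the educational intervention", with VAS rounds in three daily windows and nursing action recorded. Patients are "recruited from two surgical wards specialising in patients with a cancer diagnosis", one ward per arm, and "Assignment to either the intervention ward or control ward is done by the research team". The Secondary outcome measure section says that control-ward patients are assessed so that competing explanations can be ruled out.

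**The concern.** One outcome has two schedules that cannot both be followed. Study staff could not tell from the text when to measure patients, and an analyst could not tell what the baseline is.

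The choice matters for study question 2, which asks whether the intervention influences patients' pain. If the methods section governs, every patient on the intervention ward is admitted after its nurses have been trained. There is then no record of how patients fared on either ward beforehand. With one ward per arm and no randomisation, a lasting difference in how the wards manage pain during the stay, or in when they discharge patients, looks the same as an intervention effect. The Study design section itself concedes that the groups may differ systematically. The nurse outcome does not have this weakness, because both wards complete a baseline KAS.

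The 24-hour allowance adds a second problem. The first patient score may be taken on a ward where systematic assessment is already running.

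**Working it through.** **1. The schedules side by side**

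| Section | Patient time points | Before the education? |
|---|---|---|
| Abstract | Baseline, 4 weeks, 12 weeks | Implied by baseline |
| Secondary outcome measure | Each patient's admission (up to 24 h) and discharge | No, after the education |
| Statistical analysis | Baseline and end of study | Not defined |

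Figure 1 is not available here. It might show which schedule was meant, but the abstract and the methods text would still conflict.

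**2. What the admission score can and cannot do**

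- It can remove a difference between wards in pain at arrival.
- It cannot remove a difference that arises between admission and discharge for reasons that predate the intervention, such as usual pain care or discharge practice.
- The VAS windows are 4–6 am, 1–3 pm and 7–9 pm, so a full 24 hours contains all three. A score taken at the outer limit can follow three systematic rounds on the intervention ward and none on the control ward. If the rounds lower pain, the admission score there is already lower. The admission-to-discharge change then shrinks toward no effect.

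**3. The plan's own figure (Setting, sample and sample size considerations)**

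Inputs: difference 1.8 points on current pain, two-sided alpha 0.05, power 95%, 30 patients per group. No SD is given, so the 30 cannot be reproduced independently. The SD that it implies is

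SD = 1.8 / [(1.960 + 1.645) × √(2/30)] = 1.8 / (3.605 × 0.2582) = 1.93.

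With the t distribution it is 1.90, a standardised difference of 1.8/1.90 = 0.95.

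**4. Size of the problem (illustration only)**

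Assume no intervention effect, 30 patients per ward, an unadjusted two-sample t-test and a standing ward difference b. Then SE = 1.90 × 0.2582 = 0.491. The rejection probability comes from the noncentral t distribution with 58 degrees of freedom and noncentrality b/SE.

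| Assumed b | In SD units | b/SE | Declared significant |
|---|---|---|---|
| 0 | 0 | 0 | 5% |
| 0.57 | 0.3 | 1.16 | about 21% |
| 0.95 | 0.5 | 1.93 | about 48% |

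The values of b are assumptions; the documents give none. The same formula with SD from 1.5 to 3.0 gives about 30% down to 11% for 0.57 points, and about 67% down to 23% for 0.95 points.

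**5. What a pre-education cohort would need**

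Take separate patients in each ward and period, with the contrast being the difference in differences. Then SE = SD × √(4/n per cell), using SD 1.93.

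- n = 30 per cell: SE = 1.93 × 0.365 = 0.706; power = Φ(1.8/0.706 − 1.96) = Φ(0.59), about 72%.
- n = 60 per cell: SE = 0.499; power = Φ(3.605 − 1.96) = Φ(1.645) = 95%. That is 4 × 60 = 240 patients.

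These figures leave out ward-by-time variation, which cannot be estimated with one ward per arm.

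**The case against.** The best defence is that each patient is measured twice on both wards, and that the Statistical analysis section plans multivariate comparisons alongside demographics and diagnosis. At patient level this is a pretest–posttest design with a non-equivalent control group, as the Study design section announces. This stands. A reader might infer that question 2 rests on a post-only comparison, or that any ward difference enters the estimate in full. The documents do not support either reading, because differences in admission pain can be adjusted for. What is missing is a ward-level period before the education.

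The late admission score is a limiting case. The text says on admission, 24 hours is the outer bound, and nothing says that late completion is usual. Its bias is toward no effect, whereas a standing ward difference can act in either direction. The documents do not show which would dominate.

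A reader might also infer that a pre-education patient cohort is a cheap and obvious remedy. It is not. It would need about twice the patients per ward in each period to keep 95% power. Nurses administer the BPI-SF, and the Primary outcome measure section treats pain assessment by control-ward nurses as a possible exposure to the intervention. A pre-education phase would start that exposure earlier.

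Finally, this is the secondary outcome, non-equivalence is acknowledged, and the form of adjustment may be left to an analysis plan not shown here. All this is fair, but it does not resolve the conflicting schedules or say which baseline is meant.

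**Conclusion.** The concern holds in this form. The abstract and the methods contradict each other on when patients are measured, and the analysis section leaves the patient baseline undefined. Under the methods schedule neither ward has a pre-education patient level. Standing differences in in-stay pain care or discharge practice therefore cannot be separated from the intervention, and the admission score repairs this only in part. The primary nurse outcome is not affected.

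The rates of about 21% and 48% show what moderate standing differences could do. They rest on a back-solved SD of about 1.9, assumed ward differences and an unadjusted test. They are not estimates of bias in this trial, and the documents give no evidence that the wards do differ by these amounts.

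**What to change.** 1. **Reconcile the abstract, the Secondary outcome measure section and the Statistical analysis section.** If the admission and discharge schedule is the intended one, correct the abstract and define the patient baseline as the admission BPI-SF. Cost: wording.
2. **Protect the admission score.** Complete the admission BPI-SF before the patient's first scheduled systematic VAS round. The control ward has no such rounds, so apply the same clock-time limit there and record the completion time on both wards. Make the analysis the discharge score adjusted for the admission score. Cost: an instruction to the admitting nurses and one recorded time.
3. **Limit the claim for study question 2.** State that it is a post-education comparison of two non-equivalent wards with adjustment for admission pain, so a difference cannot be attributed to the intervention alone. Cost: wording.

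**Optional:** a pre-education patient cohort on both wards, analysed as ward by period. At the implied SD this takes about 60 patients per ward per period for 95% power; 30 gives about 72%. It also brings nurse-administered pain assessment forward and, with one ward per arm, still cannot estimate ward-by-time variation. The limit in item 3 would therefore remain in softened form.

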#### Obtaining informed consent from participants

Patients who meet the inclusion criteria on both participating surgical wards will be invited to take part in the study by the admitting RN or by the RN in charge of the patient. Both written and verbal information about the study and its protocol will be provided. All RNs on both wards will be informed verbally and in writing about the study before participating.

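### Ward nurses who know their ward's status, trained on the intervention ward, invite the patients and undertake the BPI-SF, so the secondary patient outcome is open to differential reporting and recruitment

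*Protocol article*

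**What the plan says.** All references are to the protocol article.

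- **Who is treated.** Intervention programme: the first component is "a theory-based education for ward RNs caring for patients with a cancer diagnosis". The second is guidelines for daily systematic pain assessment. Inclusion criteria: "We will include all RNs on the control ward and intervention ward"; temporary staff are excluded.
- **Who recruits.** Obtaining informed consent from participants: eligible patients on both wards "will be invited to take part in the study by the admitting RN or by the RN in charge of the patient".
- **Who collects the patient outcome.** Secondary outcome measure: "The BPI-SF will be undertaken by the RNs admitting, discharging and/or responsible for the patient". This happens within 24 hours of admission and again at discharge.
- **When.** The same section says that these assessments "will follow directly after the educational intervention for the RNs on the intervention ward and control ward".
- **Who knows the allocation.** Setting, sample and sample size considerations: "Assignment to either the intervention ward or control ward is done by the research team". There is one ward per arm.
- **What counts as exposure.** Primary outcome measure: there is a risk that "the RNs on the control ward may be inadvertently exposed to the interventions", which the article explains as their assessing patients' pain intensity and its impact on daily life. The response is to give control nurses the KAS at baseline and at twelve weeks.

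**The concern.** The BPI-SF is the only measure of study question 2, whether an intervention aimed at nurses changes patients' perception of pain, and it has its own sample size. The workshops are meant to change nurses' attitudes and practice on pain. On one ward, nurses who have just had that training invite the patients and undertake the form; on the other, untrained nurses do. Training could affect who is approached, how the form is introduced, and what a patient is willing to tell the nurse giving the care. Any of these can produce a ward difference, in either direction, with no difference in pain.

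The control ward raises a second problem. The BPI-SF records pain intensity and pain impact on daily life, which is the activity the article itself names as exposure. According to the Background section, screening for pain and systematic daily assessment are not yet standard practice on general wards in Sweden. Asking control nurses to undertake the form moves that ward some way from usual care and would tend to shrink a real effect.

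**Working it through.** **1. The passages side by side**

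| Step | Intervention ward | Control ward | Section |
|---|---|---|---|
| Workshops, guidelines, VAS three times a day | Yes | No | Intervention programme; Control intervention |
| Establishing pain by VAS at admission | Assessor not stated | Assessor not stated | Inclusion criteria |
| Invitation | Ward nurse, after training | Ward nurse, untrained | Obtaining informed consent |
| BPI-SF at admission and discharge | Ward nurse, after training | Ward nurse, untrained | Secondary outcome measure |
| KAS | Baseline, 4 and 12 weeks | Baseline and 12 weeks | Primary outcome measure |

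Both BPI-SF assessments follow the education, and the article describes no patient measurement before it. Comparing the wards on demography and diagnosis cannot show a difference in how pain is reported, or selection on something unrecorded. The KAS may hint at exposure if control scores rise. It does not record whether control nurses began assessing pain, and it does not alter the BPI-SF comparison.

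**2. The plan's BPI-SF sample size**

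Inputs from the sample size section: difference 1.8 points on current pain, two-sided alpha 0.05, power 95%, 30 per group. No SD is given, so the 30 cannot be reproduced independently; it can only be solved for the SD it implies.

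- Two-sample t-test: 30 per group and 95% power correspond to a standardised difference of 0.947, so SD = 1.8 / 0.947 = 1.90.
- Normal approximation: SD = 1.8 / (1.960 + 1.645) × √(30/2) = 1.93.

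**3. Illustration of a spurious difference (shift sizes are assumptions)**

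Suppose there is no true effect and the discharge comparison carries a pure reporting or recruitment shift b. With SD 1.90, SE = 1.90 × √(2/30) = 0.49. The chance of a significant two-sided t-test is:

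| b (points) | Rejection rate |
|---|---|
| 0 | 5% |
| 0.25 | 8% |
| 0.5 | 17% |
| 0.75 | 32% |
| 1.0 | 52% |

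The normal approximation with SD 1.93 gives the same percentages. If the SD were anywhere from 1.5 to 3.0, the rate would run from 25% down to 10% for a 0.5-point shift, and from 72% down to 25% for a 1.0-point shift.

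These rates apply to a discharge-only contrast, or to a shift that differs in full between admission and discharge. If the same shift b is present at both times, the change score is (discharge + b) − (admission + b) = discharge − admission, and b drops out.

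**4. Illustration of dilution on the control ward (dilution sizes are assumptions)**

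| Dilution | Remaining difference | Power at 30 per group |
|---|---|---|
| 0% | 1.80 | 95% |
| 10% | 1.62 | 90% |
| 20% | 1.44 | 82% |
| 30% | 1.26 | 71% |
| 50% | 0.90 | 44% |

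Dilution pulls towards zero and a reporting shift may go either way, so the net bias cannot be signed in advance.

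**The case against.** The strongest reply is that this is a secondary outcome in an openly non-randomised study. The KAS is answered by the nurses and is untouched by how patients are recruited or report pain. With one ward per arm the patient comparison is already confounded with ward, and a different way of collecting the form does not change that. This stands and lowers the severity.

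Several stronger readings are tempting, but the article does not support them:

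- *Trained nurses carry out the screening VAS and choose the patients.* The Inclusion criteria do not say who does the screen, and they fix the rule that patients scoring above 1 are invited. The text gives nurses the invitation, not discretion. That some discretion remains in practice is an inference.
- *Nurses interview the patients.* Both instruments are patient ratings: the patient marks the VAS line and the body figure. The wording for the BPI-SF leaves open whether the nurse asks the questions or hands over a form. An influence through how questions are put depends on which is meant; reporting to one's own nurse is possible either way.
- *The control ward receives the core of the intervention.* Its exposure is partial: the BPI-SF at two time points and possibly the VAS screen, without workshops, guidelines or the VAS three times a day.
- *The false-positive rate of this trial is 17% or 52%.* Those figures follow from assumed shifts and a back-solved SD, and a constant shift would largely cancel in a change from admission to discharge.

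The article does acknowledge contamination and adds a check. What remains is that the check looks at knowledge and attitudes, while the exposure it worries about is partly built into its own data collection.

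**Conclusion.** The point holds in limited form and is **should-fix**. The article itself assigns invitation and BPI-SF collection to the ward nurses, after the education and with ward status known. The secondary patient outcome is therefore open to differential reporting and recruitment, and the control ward is partially exposed to an activity that the article counts as exposure. The 12-week KAS neither prevents nor corrects either problem.

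The size of the bias cannot be derived from the document. The 17% and 52% figures show only what an assumed 0.5- or 1.0-point spurious discharge difference would do at 30 per group with an SD of 1.90. No sample size figure is shown to be wrong, and the nurse-reported primary outcome is not affected by patient recruitment or reporting. Control-ward exposure could in principle also dilute the KAS contrast, but nothing in the article allows that to be quantified.

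**What to change.** 1. **BPI-SF.** Change Secondary outcome measure so that the patient completes the form alone on paper at admission and at discharge, with the same written instructions on both wards, and returns it sealed to the research team.
2. **Screening VAS.** Keep it patient-marked but unsealed. If it were sealed as well, the ward nurse could not apply the rule of a score above 1 and could not invite the patient.
3. **Recruitment.** State that consecutive eligible admissions are approached, and keep a per-ward log of patients screened, eligible, invited and consenting. The log documents selective recruitment but does not remove it, because ward nurses still make the invitation.

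Cost: envelopes, one instruction sheet and a one-page log, with no extra ward staff. The downside is some missing items from patients who need help with the form. Some control-ward exposure remains through the screening VAS and handing out the form. The change has to be made before patients are enrolled, since analysis cannot separate a reporting shift that differs between wards from a real difference in pain.
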